#### Main analysis

The primary analysis approach for the primary outcome of composite of adverse fetal/neonatal outcomes, maternal secondary outcomes and the Infant Health Questionnaire will be intention to treat with participants analysed in the groups to which they are assigned regardless of deviation from the protocol or intervention received. The PARCA-R will be both an intention to treat and a per protocol analysis, since the hypothesis under examination for these outcomes is a non-inferiority hypothesis. The per-protocol analysis will exclude babies of women who do not receive their intervention as planned. As the trial includes multiple centres (and will involve a reasonable number of participants randomised per centre), the analysis will be based on the individual participant, allowing for clustering between participants within centre using robust SEs. All analyses will additionally adjust for gestational age at inclusion (stratification risk factor used in randomisation) as a fixed factor. For binary outcomes (composite of adverse fetal/neonatal outcomes, gestational hypertension, pre-eclampsia) a logistic regression model will be used to compare this outcome by arm and results presented as ORs and two-sided 95% CI. Continuous outcomes (PARCA-R, Infant Health Questionnaire) will be analysed using linear regression and results presented as adjusted differences in means alongside 95% CIs. The Infant Health Questionnaire will also be examined over time using a repeated measures model, and will include an interaction term for time (6, 12, 18 and 24 months) and trial arm to investigate any divergent or convergent pattern in Infant Health Questionnaire. The categorical outcomes of mode of delivery and onset of labour will be compared between trial arms by fitting a multilevel ordinal regression model. The neonatal secondary outcome will be examined using the mean PARCA-R score between each trial arm using linear regression, and a one-sided 95% CI constructed to assess non-inferiority. Additional pre-specified sub-group analyses will be carried out to analyse the primary outcome in the whole cohort by those that are <10th percentile (vs ≥10th) and <3rd percentile (vs ≥3rd) based on different growth charts, maternal morbidity (yes/no) and corticosteroid administration (yes/no).^22 23^ If numbers are sufficient, we will also describe the intervention effect in the subgroups <3rd percentile versus 4–10th vs >10th percentile but will not statistically test for intervention effect.

All analyses will be undertaken after database lock following data collection at 2 years. No interim analyses are planned. Missing outcome data but will be accounted for in sensitivity analyses using multiple imputation, where we will assume that outcome data are missing at random given the observed measurements. All planned analyses will be described in detail in a statistical analysis plan, which will be finalised prior to database lock. The reporting of findings will be in accordance with the Consolidated Standards of Reporting Trials guidelines for Randomized Controlled Trials (RCTs). Statistical analysis will be performed in Stata (V.16 or higher).

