**Methods and analysis:**

Women with non-anomalous singleton pregnancies 32+0 to 36+6 weeks of gestation in whom the estimated fetal weight or abdominal circumference is <10th percentile or has decreased by 50 percentiles since 18–32 weeks will be included for observational data collection. Participants will be randomised if cerebral blood flow redistribution is identified, based on umbilical to middle cerebral artery pulsatility index ratio values. Computerised cardiotocography (cCTG) must show normal fetal heart rate short term variation (≥4.5 msec) and absence of decelerations at randomisation. Randomisation will be 1:1 to immediate delivery or delayed delivery (based on cCTG abnormalities or other worsening fetal condition). The primary outcome is poor condition at birth and/or fetal or neonatal death and/or major neonatal morbidity, the secondary non-inferiority outcome is 2-year infant general health and neurodevelopmental outcome based on the Parent Report of Children’s Abilities-Revised questionnaire.

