#### Eligible for randomisation: consent for randomisation

Consent for randomisation once cerebral redistribution is identified, with UCR (as defined above) of ≥1.0 at 32+0 to 33+6 weeks and ≥0.8 at 34+0 to 36+6 weeks. This consent will also include contact details and willingness to be contacted in the future for follow-up data collection (online supplemental file 3—consent for randomisation).

10.1136/bmjopen-2021-055543.supp3Supplementary data

Women are randomly allocated to either immediate delivery or delayed delivery as defined below. Randomisation has a 1:1 allocation ratio and stratified based on gestational age (above or below 34 weeks) and centre. Randomisation is conducted on the electronic data capture platform (Castor EDC, Amsterdam, The Netherlands).

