### Statistics and data analysis

#### Sample size

The trial is powered to detect if immediate delivery following cerebral redistribution is superior to expectant management following cerebral redistribution on this outcome. A difference in the proportion with the primary outcome from 15% in the delayed delivery to 9% in the immediate delivery (from TRUFFLE 2 feasibility study) demonstrates an OR of 0.56. At two-sided 5% significance with 95% power, 780 participants per arm are required, giving 1560 in total. Given the immediacy of this outcome, no loss to follow-up is expected. An important non-inferiority secondary safety outcome is infant neurodevelopment, which is measured by parent completed questionnaire at 2 years using the PARCA-R, as recommended in NICE Guidance,^21^ supplemented by infant health information over the intervening 2 years. Assuming a loss to follow-up at 2 years of 20%, 2-year outcomes for approximately 1248 infants are expected (624 per group assuming no difference in the lost to follow-up between the groups). The PARCA-R questionnaire provides a composite score for neurodevelopment with a standardised mean of 100 and SD of 15. With a one-sided significance level of 1%, under a non-inferiority hypothesis, a sample size of 624 in each group achieves a 98% power to detect a non-inferiority margin of difference in the mean PARCA-R score of no less than four points (0.25 of a SD). A margin of no less than three points can be detected with 90% power.

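### Adjusting for gestational age only through the 34-week stratum is valid, but adding exact gestation at randomisation as a continuous covariate would give a small, free gain in precision

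*Protocol article*

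**What the plan says.** Under Main analysis, the protocol article fixes one covariate for every model: "All analyses will additionally adjust for gestational age at inclusion (stratification risk factor used in randomisation) as a fixed factor". The section on consent for randomisation says that allocation is "stratified based on gestational age (above or below 34 weeks) and centre". Study design places randomisation at the second qualifying Doppler ratio measurement. Together these identify the covariate as the 34-week stratum, although Main analysis does not itself give the number of levels.

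The words for entry are used in two senses. In the abstract, women who meet the fetal-size criteria "will be included for observational data collection" and are randomised only if redistribution is then found. The section headed Inclusion criteria, by contrast, lists the conditions for randomisation itself.

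The primary outcome is planned without any covariate: "A difference in the proportion with the primary outcome from 15% in the delayed delivery to 9% in the immediate delivery", and "At two-sided 5% significance with 95% power, 780 participants per arm are required, giving 1560 in total".

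**The concern.** A two-level factor treats all women in the lower stratum (two weeks wide) as alike, and likewise all women in the upper stratum (three weeks wide). The primary composite includes components that plausibly depend on prematurity within those bands, such as respiratory support, treated patent ductus and surgical necrotising enterocolitis. If so, part of the explainable variation in outcome is left in the error, and chance imbalance in gestation within a stratum is not adjusted away. What is at stake is precision, not bias.

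The label for the covariate is also loose. A woman may enter observation at 33 weeks and be randomised at 35, so gestation at observational entry and gestation at randomisation can fall on different sides of the cut. Someone building the analysis dataset should not have to work out which date is meant.

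**Working it through.** **1. The plan's own figure.** Inputs from Sample size: 15% versus 9%, two-sided 5%, 95% power, no loss to follow-up. The mean proportion is 0.12.

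n per arm = [1.960 × √(2 × 0.12 × 0.88) + 1.645 × √(0.15 × 0.85 + 0.09 × 0.91)]² / 0.06²
= [1.960 × 0.4596 + 1.645 × 0.4576]² / 0.0036
= 1.6534² / 0.0036 ≈ 759.4, so 760 per arm.

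With continuity correction the figure is 793. The stated 780 lies between the two, within 3% of each, and 780 per arm gives 95.5% power. The odds ratio is (0.09/0.91)/(0.15/0.85) = 0.560, matching the stated 0.56. The calculation contains no covariate, so the choice of covariate does not change the required number.

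**2. Assumptions for the covariate question.** The documents give neither the prognostic strength of gestation nor its distribution among randomised women. Assumed here: gestation uniform over 32 to 37 weeks, log-odds of the outcome linear in gestation with slope b per week, marginal risks of 15% and 9%, N = 1560, and 1:1 allocation within the two strata. Centre and robust standard errors are not modelled.

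**3. Large-sample comparison.** For each slope, fit the logistic model with (i) treatment and stratum and (ii) treatment, stratum and continuous gestation. Take z = expected treatment coefficient / its standard error.

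Gain in effective sample size = (z₂/z₁)² − 1. Power = Φ(z − 1.960).

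| b per week | OR per week | z₁ (stratum) | z₂ (plus gestation) | Gain | Power, % |
|---|---|---|---|---|---|
| −0.2 | 0.82 | 3.623 | 3.627 | 0.2% | 95.18 → 95.22 |
| −0.3 | 0.74 | 3.637 | 3.646 | 0.5% | 95.32 → 95.41 |
| −0.5 | 0.61 | 3.679 | 3.702 | 1.2% | 95.72 → 95.92 |
| −0.7 | 0.50 | 3.733 | 3.777 | 2.4% | 96.18 → 96.54 |

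For the last row, (3.7767/3.7325)² − 1 = 0.024, or about 1560 × 0.024 ≈ 37 women.

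**4. Simulation cross-checks.** Two simulations under the same assumptions agree.

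- Adding gestation to the stratum (2500 trials per setting, slopes −0.3 to −0.7) gave gains of 0.5% to 2.8%, with power moving from 94.8% to 94.9%, 96.3% to 96.5% and 96.7% to 97.1%.
- Replacing the stratum by linear gestation (3000 trials per setting) gave gains of 0.3%, 0.7%, 1.1%, 2.1% and 4.1% for an odds ratio per week of 0.8, 0.7, 0.6, 0.5 and 0.4. Power changed by between −0.1 and +0.5 points. The standard error of one simulated power near 95.5% is √(0.955 × 0.045/3000) ≈ 0.4 points, so these power differences are no larger than simulation noise and the efficiency ratio is the steadier measure.

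The 4.1% needs control risk of about 50% at 32 weeks falling to about 1% near 37 weeks, and is not used in the stated range.

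**The case against.** The strongest reply is that nothing here is wrong. Adjusting for the stratification factor as randomised is standard, chance imbalance within strata does not bias a randomised comparison, and the confidence interval already allows for it. The article also defers detailed analyses to a statistical analysis plan, which could add exact gestation. All of this stands, and for that reason the point is an improvement and not a correction.

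Two of the premises are inferences, as the objection would rightly say. No section quantifies how prognostic gestation is, and the composite also contains hypoxia-related components. A slope of −0.7 per week is already steep: exp(0.7 × 5) ≈ 33-fold in odds over five weeks. Nor does any section name exact gestation at randomisation as a recorded variable. Eligibility limits given in weeks and days, with eligibility data entered in the trial database, make it very likely to be derivable.

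A reader might go further and infer from *at inclusion* that the model would adjust for a different variable from the one used to stratify. The documents do not support this. The parenthesis in the quoted sentence says that the covariate is the stratification factor, Study design applies stratification at randomisation, and the Inclusion criteria are the criteria for randomisation. Only the wording is loose.

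**Conclusion.** The planned adjustment is valid and the sample size is unaffected. Under the natural two-level reading, it leaves some available information unused. Recovering it is worth about 0.2% to 3% in effective sample size and less than 0.5 points of power at the planned effect, for assumed slopes of −0.2 to −0.7 per week with gestation uniform over 32 to 37 weeks. A non-linear gradient or another distribution would shift these figures somewhat, and a weaker gradient would bring the gain close to zero. The gain for the 2-year developmental score was not computed, because no correlation with gestation is given. This is a minor point, worth taking because it costs almost nothing.

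**What to change.** Reword the sentence so that all analyses adjust for the gestational-age stratum as used at randomisation and, in addition, for exact gestational age at randomisation (in days) as a continuous covariate. Replace *at inclusion* with *at randomisation*.

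The cost is one sentence, in a protocol update or in the statistical analysis plan, which is due to be finalised before database lock. It needs no new data collection, provided that exact gestation at randomisation is confirmed to be derivable from the database. The choice should be fixed before outcomes are seen by arm, because in a logistic model an added prognostic covariate slightly changes which conditional odds ratio is estimated.

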#### Secondary outcomes

##### For the baby

Health and developmental outcomes—assessed using Parent Report of Children’s Abilities-Revised (PARCA-R) questionnaire at 2 years corrected age and an Infant Health Questionnaire up to 2 years (online supplemental file 4—PARCA-R Questionnaire and online supplemental file 5—Infant Health Questionaire).

10.1136/bmjopen-2021-055543.supp4Supplementary data

10.1136/bmjopen-2021-055543.supp5Supplementary data

The PARCA-R^18^ will be completed at 24 months term-equivalent age, this allows derivation of the non-verbal cognitive scale and language development scale. Raw scores from the scales are standardised (by corrected age and gender) to a notional population mean of 100 (SD=15) and the average of these two component scores will be taken as the overall composite score. Corrected age is used for preterm babies (born before 37 weeks) and represents the age of the child from the estimated date of delivery.

The Infant Health Questionnaire^19^ will be used to derive the following health outcomes at 6, 12, 18 and 24 months post partum:

Use of any hospital service (yes/no) and total number of contacts over the 2-year period.Admitted to hospital (yes/no) and total number of admissions over the 2-year period.Planned/unplanned admissions to hospital (yes/no) over the 2-year period.Intensive care or not over the 2-year period.Attended emergency department (and not subsequently admitted) (yes/no) over the 2-year period.Attended Outpatients/clinic (yes/no) over the 2-year period.

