##### For the mother

Gestational hypertension developed post study entryAs defined by the International Society for Study of Hypertension in pregnancy (ISSHP):^20^ hypertension (blood pressure ≥140/90 mm Hg) arising de novo after 20 weeks gestation in the absence of proteinuria.Pre-eclampsia developed post study entryAs defined by the ISSHP:^20^ blood pressure ≥140/90 mm Hg and significant proteinuria (protein/creatinine ratio of 30 mg/mmol or more).Onset of labour (spontaneous, induction (method), prelabour caesarean section).Mode of delivery (spontaneous vaginal, assisted vaginal, caesarean section).

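### The Infant Health Questionnaire is analysed as continuous although only yes/no items and counts are derived from it, and onset of labour is given an ordinal model that one common odds ratio cannot credibly summarise

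*Protocol article*

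**What the plan says.** **Infant Health Questionnaire.** The Main analysis section of the protocol article states: "Continuous outcomes (PARCA-R, Infant Health Questionnaire) will be analysed using linear regression", with the effect reported as an adjusted mean difference and its 95% CI. It adds a repeated measures model with an arm-by-time interaction at 6, 12, 18 and 24 months, without naming a distribution or link.

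The list of secondary outcomes for the baby says what the questionnaire yields. Two entries pair a yes/no item with a total: "Use of any hospital service (yes/no) and total number of contacts over the 2-year period" and "Admitted to hospital (yes/no) and total number of admissions over the 2-year period". The others are yes/no only, for example "Attended emergency department (and not subsequently admitted) (yes/no) over the 2-year period".

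For binary outcomes the plan has its own rule: "For binary outcomes (composite of adverse fetal/neonatal outcomes, gestational hypertension, pre-eclampsia) a logistic regression model will be used". No questionnaire item is in that list.

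**Delivery outcomes.** The Main analysis section states: "The categorical outcomes of mode of delivery and onset of labour will be compared between trial arms by fitting a multilevel ordinal regression model". The maternal outcome list defines the first of these as "Onset of labour (spontaneous, induction (method), prelabour caesarean section" and gives no ranking. Under Immediate delivery, the allocated treatment is caesarean birth or the start of induction within 48 hours. Under Delayed delivery, women are monitored and delivered on stated triggers, or by local plan from 37+0 weeks.

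**The concern.** The model assigned to the questionnaire presupposes a continuous score that the outcome list never defines. An analyst must either report mean differences for 0/1 items, while every other binary outcome is reported as an odds ratio, or depart from the published plan. The questionnaire is not incidental: the Assessment and follow-up section places it among the key secondary infant outcomes, and the sample size section uses infant health information to supplement the PARCA-R safety outcome.

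For onset of labour, an ordinal model reports one odds ratio assumed equal at every cut of the scale. Allocation itself pushes the first cut (spontaneous versus not) strongly in one direction. The second cut (prelabour caesarean versus the rest) reflects how clinicians divide women between induction and caesarean, which is a different question. A single number blends the two and also depends on how the categories are ranked.

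**Working it through.** The plan states no rates or effect sizes for these outcomes, so there is no figure of its own to reproduce. The check has three parts.

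**1. Outcome type against assigned model (questionnaire)**

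| Derived outcome | Type | Model under the plan's binary rule | Model assigned |
|---|---|---|---|
| Any hospital service; contacts | binary; count | logistic; none stated for counts | linear |
| Admission; number of admissions | binary; count | logistic; none stated for counts | linear |
| Planned/unplanned admission | binary | logistic | linear |
| Intensive care | binary | logistic | linear |
| Emergency attendance without admission | binary | logistic | linear |
| Outpatient attendance | binary | logistic | linear |

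All six entries contain a yes/no item, two add a count, and none is continuous.

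**2. Does linear regression give a wrong answer for the yes/no items?**

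For a 0/1 outcome the arm coefficient is the risk difference p1 − p0. The unadjusted robust standard error is √[p0(1−p0)/n + p1(1−p1)/n]. With n = 624 per arm (the plan's figure after 20% loss), 4,000 simulated trials and assumed proportions, coverage of the 95% interval was:
- 5% v 8%: 0.9495
- 20% v 20%: 0.9508
- 30% v 36%: 0.9485

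Coverage is nominal. Clustering by centre was not simulated.

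**3. Cut-point odds ratios for onset of labour**

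The protocol gives no onset rates, so every distribution here is an assumption. Rank the categories spontaneous < induction < prelabour caesarean. At each cut, OR = [P/(1−P)] in the immediate arm ÷ [P/(1−P)] in the delayed arm, where P is the proportion above the cut.

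First cut, with 2% spontaneous onset in the immediate arm:
- delayed arm 5%: (0.98/0.02)/(0.95/0.05) = 49/19 = 2.6
- delayed arm 20%: (0.98/0.02)/(0.80/0.20) = 49/4 = 12.25, about 12.3

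Second cut, with prelabour caesarean in 50% (immediate) v 40% (delayed): (0.50/0.50)/(0.40/0.60) = 1.5.

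The two cuts therefore differ by a factor of 2.58/1.5 = 1.7 at the low end and 12.25/1.5 = 8.2 at the high end.

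A proportional-odds model was also fitted to four assumed distributions (spontaneous/induction/caesarean, %), with 780 per arm:

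| Immediate | Delayed | First-cut OR | Second-cut OR | Common OR (95% CI) | Common OR if induction is ranked lowest |
|---|---|---|---|---|---|
| 2/58/40 | 15/35/50 | 8.6 | 0.67 | 0.93 (0.77 to 1.12) | 0.51 |
| 1/59/40 | 10/45/45 | 11.0 | 0.81 | 1.02 (0.84 to 1.24) | 0.67 |
| 2/48/50 | 25/35/40 | 16.3 | 1.50 | 2.18 (1.80 to 2.65) | 0.95 |
| 2/68/30 | 10/45/45 | 5.4 | 0.52 | 0.70 (0.57 to 0.85) | 0.43 |

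First row: (0.98/0.02)/(0.85/0.15) = 8.6 and (0.40/0.60)/(0.50/0.50) = 0.67. These two opposing effects collapse to 0.93, which would read as no difference. In three of the four rows the cuts point in opposite directions. In every row the common OR changes materially with the ranking, which the plan does not state.

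**The case against.** **The linear model is defensible.** A mean difference on a 0/1 item is a risk difference, and on a count it is a difference in mean contacts or admissions. Both are legitimate estimands, and robust standard errors are planned. This stands. A reader might infer that the planned models fail to estimate the listed outcomes or give biased tests; the coverage check does not support that. Skewed counts are an efficiency and reporting matter, and negative binomial is one reasonable choice among several. What remains is the contradiction between the outcome definitions and the label, and the mixed effect measures.

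**The repeated measures model is not said to be linear.** Correct. One might read linear trends on 0/1 items into the text, but no link, distribution or trend is given. The only request is that the link match the outcome type.

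**Mode of delivery.** It is tempting to say that the design breaks the ordinal model here too. It does not: allocation fixes how birth is initiated in the immediate arm, not whether it ends as spontaneous vaginal, assisted vaginal or caesarean. Those categories can be read as increasing intervention. Mode is also a separate listed outcome, so the question of extra caesareans does not depend on the onset model.

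**The size for onset is assumed.** This also stands. Delayed-arm delivery is often triggered by monitoring or by local plans at term, so spontaneous onset there could be rare and the first-cut odds ratio modest. The four fitted scenarios use 10% to 25% spontaneous onset in the delayed arm and so show larger discordance.

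**A later statistical analysis plan may refine this.** It may, but the article assigns these models explicitly. This is stated text that conflicts, not a detail left out.

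**Conclusion.** The point holds in two limited parts.

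- **Questionnaire:** the Main analysis section contradicts the outcome list and its own rule for binary outcomes. All six derived entries are affected. The consequence is a wrong outcome type and an inconsistent effect measure; inference on the arm difference remains valid with robust standard errors, as far as a check without centre clustering shows.
- **Onset of labour:** a single common odds ratio is not credible, because the categories carry no stated order and allocation nearly empties one of them in one arm. The direction of this argument follows from the protocol; its size does not. With 2% spontaneous onset assumed in the immediate arm, the first-cut odds ratio runs from 2.6 (5% in the delayed arm) to 12.3 (20%).

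All affected outcomes are secondary and have no power statement. The primary composite, the PARCA-R analysis and the sample size are unaffected. The correction should be made before database lock, but it does not threaten the trial's main conclusion.

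**What to change.** In the Main analysis section, and in the statistical analysis plan before database lock:

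1. Remove the Infant Health Questionnaire from the continuous outcomes. Analyse each yes/no item by logistic regression, or by a risk-difference model declared as such.
2. Analyse total contacts and total admissions with a count model such as negative binomial.
3. For the 6, 12, 18 and 24-month model, state a link that matches each outcome (logit for yes/no items, log for counts).
4. Analyse onset of labour by multinomial logistic regression, or report percentages by arm.
5. For mode of delivery, either keep the ordinal model with the category order stated and proportional odds checked, or report caesarean versus vaginal birth.

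The cost is wording. All these models are standard in Stata, which the plan already names, and no new data or change in sample size is needed.

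### The PARCA-R non-inferiority test is powered at a one-sided 1% level but will be judged with a one-sided 95% interval, which is a 5% test

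*Protocol article*

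**What the plan says.** Two sections of the protocol article set the error level for the PARCA-R comparison.

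- **Sample size:** "With a one-sided significance level of 1%, under a non-inferiority hypothesis", with 98% power for a "non-inferiority margin of difference in the mean PARCA-R score of no less than four points (0.25 of a SD") and 90% power for a 3-point margin. The inputs are "2-year outcomes for approximately 1248 infants are expected (624 per group") and "a standardised mean of 100 and SD of 15".
- **Main analysis:** the mean PARCA-R score is compared between arms by linear regression, with "a one-sided 95% CI constructed to assess non-inferiority". PARCA-R is analysed both by intention to treat and per protocol.

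For continuous outcomes in general, PARCA-R among them, Main analysis also has "results presented as adjusted differences in means alongside 95% CIs", without saying whether these are one- or two-sided. The article does not say that the 1% level was superseded, or that it was meant for planning only.

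**The concern.** A one-sided 1% test corresponds to a one-sided 99% confidence bound, the lower limit of a two-sided 98% interval. A one-sided 95% bound is a 5% test. The two sections therefore give different decision rules for one hypothesis, and a single data set can be non-inferior under one and not under the other.

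PARCA-R is a secondary outcome, but it carries the safety half of the trial hypothesis in the Abstract: that earlier delivery does not worsen neurodevelopment at two years. The error at stake is declaring that safety wrongly, and the analysis section is the looser of the two rules. The article fixes both levels itself, so this is a contradiction and not a detail left to the statistical analysis plan. An author of that plan could follow either section and claim to follow the protocol.

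**Working it through.** **Inputs** (Sample size section unless stated)

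- Allocation 1:1 (section on consent for randomisation). Two-year loss 20%: 1560 × 0.8 = 1248, or 624 per arm.
- SD 15.
- Margins: 4 points; 0.25 SD = 0.25 × 15 = 3.75 points; 3 points. The text equates 4 points with 0.25 SD, but 4/15 = 0.267. All three are carried because the article does not name the deciding one.
- Planning level: one-sided 1%. Decision interval: one-sided 95% (Main analysis), so one-sided 5%.
- My assumptions: true difference zero for power, normal approximation, no allowance for centre clustering or adjustment for gestational age.

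**Step 1: reproduce the stated powers.**

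SE = 15 × √(2/624) = 0.849 points. Power = Φ(margin/SE − z), with z = 2.326 (1%), 1.960 (2.5%) and 1.645 (5%).

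| Margin | Stated | One-sided 1% | One-sided 2.5% | One-sided 5% |
|---|---|---|---|---|
| 4 | 98% | 99.1% | 99.7% | 99.9% |
| 3.75 (0.25 SD) | 98% (same statement) | 98.2% | 99.3% | 99.7% |
| 3 | 90% | 88.6% | 94.2% | 97.1% |

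For example, at margin 3 and 1%: 3/0.849 − 2.326 = 1.206, and Φ(1.206) = 88.6%. The stated 98% is met at 0.25 SD, and the stated 90% is within 1.4 points. At one-sided 0.5% the 3-point power would be 83.1%. Of these levels only 1% comes close to both stated powers, so the 1% was really used and is not a misprint for 5%.

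**Step 2: maximum type I error.**

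When the true deficit equals the margin, the chance of declaring non-inferiority is the one-sided level itself: 1 − 0.99 = 1% under Sample size and 1 − 0.95 = 5% under Main analysis.

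**Step 3: where the two rules disagree.**

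Non-inferiority is declared when the observed deficit is below margin − z × SE. The half-widths are 2.326 × 0.849 = 1.976 (99% bound) and 1.645 × 0.849 = 1.397 (95% bound).

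| Margin | Largest passing deficit, 1% rule | Largest passing deficit, 5% rule |
|---|---|---|
| 4 | 4 − 1.976 = 2.02 | 4 − 1.397 = 2.60 |
| 3.75 | 3.75 − 1.976 = 1.77 | 3.75 − 1.397 = 2.35 |
| 3 | 3 − 1.976 = 1.02 | 3 − 1.397 = 1.60 |

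The zone of disagreement is 1.976 − 1.397 = 0.58 points wide whichever margin applies.

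**The case against.** The best defence is that 1% appears only in the power calculation, while the only stated decision rule is the one-sided 95% interval. A stricter planning level could be a deliberate allowance. Under the analysis rule power rises, and the total of 1560 comes from the primary outcome, so the trial is not underpowered for PARCA-R. The outcome is secondary, no analysis takes place before database lock, and an analysis plan is due before then.

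The points about power and sample size stand. The allowance is possible, but the article does not state it, and a later plan cannot follow two conflicting levels at once.

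Two stronger readings are tempting and should not be made.

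- **Three error levels.** A reader might take the 95% intervals for continuous outcomes as two-sided and count a third level of 2.5%. Main analysis attaches the word two-sided only to the binary outcomes. Even if these intervals are two-sided, the sentence concerns presentation and sets no non-inferiority rule. Showing such an interval beside a one-sided bound is ordinary practice.
- **An inferior policy accepted five times as often in general.** The ratio of 5 holds only when the true deficit equals the margin. At a true deficit of 5 points with a 4-point margin, the risks are Φ((2.60 − 5)/0.849), about 0.24%, and Φ((2.02 − 5)/0.849), about 0.02%. The ratio is then about 10, but both risks are tiny.

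The article also does not say whether the intention-to-treat and per-protocol analyses must both succeed. If they must, 5% is an upper limit on the joint risk. The mismatch of levels remains.

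**Conclusion.** The point holds as a contradiction between two sections: 1% one-sided in planning, 5% one-sided in the decision. Following the analysis section raises the maximum type I error for a single analysis from 1% to 5% and leaves the quoted 98% and 90% powers attached to a test that will not be run. Which results are affected depends on the margin: observed deficits of about 2.0 to 2.6, 1.8 to 2.4 or 1.0 to 1.6 points for margins of 4, 3.75 and 3. Those limits rest on SD 15, 624 per arm and an unadjusted, unclustered standard error, so they are approximate. The 1% against 5% mismatch depends on none of these. The primary outcome and the trial's size are unaffected. Because the conflict is in the decision threshold for the key safety claim, it should be settled before database lock.

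**What to change.** Use one level in both sections, by either route.

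1. **Keep 1%.** In Main analysis, replace the one-sided 95% interval with a one-sided 99% confidence bound (the lower limit of a two-sided 98% interval), for both the intention-to-treat and the per-protocol analysis. The stated powers then belong to the test that is run. The decision half-width grows from about 1.40 to 1.98 points.
2. **Keep 5%, or choose another level.** Change the level in Sample size and restate both powers. On the assumptions above, one-sided 5% gives 99.9% (4 points), 99.7% (3.75 points) and 97.1% (3 points); one-sided 2.5% gives 99.7%, 99.3% and 94.2%. The cost is an openly less strict standard for the safety claim.

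Either route takes a short amendment to the protocol, carried into the analysis plan, and no extra participants. The restated text should also name the margin to which the bound is compared, since the affected range moves with it.
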